# Use of a Therapeutic, Socially Assistive Pet Robot (PARO) in Improving Mood and Stimulating Social Interaction and Communication for People With Dementia: Study Protocol for a Randomized Controlled Trial

**DOI:** 10.2196/resprot.4189

**Published:** 2015-05-01

**Keywords:** dementia, elderly, PARO, randomized controlled trial, robot-assisted therapy, socially assistive robots

## Abstract

**Background:**

Socially assistive robotics is a growing area for geriatric research.

**Objective:**

This single-blind, randomized controlled trial (RCT) aims to investigate the use of PARO, a therapeutic, socially assistive pet robot, in improving mood, and stimulating social interaction and communication for people with dementia in the community.

**Methods:**

For the study, 40 community-dwelling older Chinese adults (≥60 years) with mild to moderate dementia will be recruited and randomly assigned to the PARO therapy group or the psychosocial activities control group. Both treatments consist of six, 30-minute weekly sessions, which will be conducted in a geriatric day hospital. Subjects in both groups will be assessed by a trained research assistant at baseline (pre-), during, and post-treatment. Mood (assessed with a simplified face scale), social interaction, and communication (ie, facial expressions and reactions towards each treatment, assessed with an observation table) will be the primary outcome measures. Secondary outcome measures will include assessments on cognitive function (Mini-Mental State Examination) and depressive symptoms (Cornell Scale for Depression in Dementia), as well as caregiver burden (Zarit Burden Inventory). Subjective impression towards each treatment and qualitative comments from the caregivers, facilitator, and therapists will also be obtained.

**Results:**

Recruitment to the pilot study began in 2014 and the last subject is expected to complete their post-treatment assessment in 2015.

**Conclusions:**

This will be the first RCT using PARO to improve mood, and stimulate social interaction and communication in the care of older people with dementia, as well as provide an evidence basis for the use of PARO in dementia care in Hong Kong.

**Trial Registration:**

The Australian New Zealand Clinical Trials Registry (ANZCTR): ACTRN12614000037606; https://www.anzctr.org.au/Trial/Registration/TrialReview.aspx?ACTRN=12614000037606 (Archived by WebCite at http://www.webcitation.org/6Xi7uXdu9).

## Introduction

With a rapidly ageing population, dementia has become an important public health issue worldwide [1]. In Hong Kong, there are over one million people aged 60 and above who had dementia in 2009, and by the year 2039, this is projected to increase to over three million [2]. Non-pharmacological interventions are recommended as the preferred first-line treatment for people with dementia [3,4], with cognitive stimulation therapy being the most studied [5]. The finding from a recent systematic review of cognitive stimulation therapy on optimizing cognitive function of older adults with mild to moderate dementia was comparatively robust and promising. However, the majority of studies have focused on cognitive abilities (eg, memory performance, problem solving, and communication techniques), and the effects on psychological and social aspects remain inconclusive [6,7].

Activities, especially in group settings such as social support groups, may be of psychological and social benefits to people with dementia by reducing depression and improving quality of life [8]. Yet, a great challenge remains with respect to how to stimulate these older people to respond and participate in such activities. Furthermore, owing to a lack of manpower for many day care centres in Hong Kong [9], few provide stimulating social activities for those with dementia. As a result, older adults with dementia spend most of the time sitting around in an environment that is not home, only effectively providing respite care for their family caregivers. Inadequate social engagement can be detrimental, as it magnifies the feelings of loneliness that often accompany the progression of dementia [10]. Other studies have also associated low social engagement with cognitive decline [11] and increased mortality [12].

In recent years, socially assistive robots have been developed for elderly care, particularly companion robots [13,14]. Anecdotal reports, as well as two systematic reviews to date, suggest that robot-assisted therapy is a potentially cost-effective treatment for dementia as it has the potential to improve mood, encourage social interaction and communication, and therefore enhance the well-being of the elderly, and decrease the workload of their caregivers [15,16]. Furthermore, the reported psychosocial effects have been more striking than the results achieved by conventional therapies [17].

Amongst the recent literature on the use of socially assistive robots in elderly care, the most widely studied is PARO (Figure 1). PARO is a therapeutic, socially assistive pet-type robot with an appearance of a baby harp seal, and is equipped with different kinds of sensors, including tactile, light, audition, temperature, and posture. Thus, it can respond to different stimulations (eg, striking and holding) given by the users, or recognize the direction of voice from them. It was designed by Shibata et al [18], and has been used with positive and promising results since 2003 in many countries including Japan, Denmark, Canada, Italy, and the United States [19-22]. In 2009, PARO was certified as a type of neurological therapeutic device by the Food and Drug Administration (FDA) in the United States (Registration number: 3009118691) [23]. In 2010, a caregiver’s manual for robot therapy was published to achieve effective therapy [24,25].

Several intervention trials demonstrated promising effects of participating in PARO therapy in increasing motivation, improving mood, reducing stress, and increasing social communication in elderly people [22,26-28]. Positive effects of PARO therapy on mood, social interaction and communication, as well as cortical neuron activity have also been reported in people with dementia [21,29,30]. A recent pilot randomized controlled trial (RCT) reported that for older people with dementia, PARO therapy had a moderate to large positive influence on their quality of life [31]. More recently, the potential therapeutic benefits of PARO for the treatment of neurological diseases have also been published [32]. Although positive effects of PARO therapy in people with dementia or other brain disorders have been reported in various populations, many were observational studies or involved small numbers of subjects. Other interventions, such as animal-assisted therapy, appeared to have beneficial effects on mood, and increased social interaction and communication in people with dementia [33-35]. However, there are many concerns with animal-assisted therapy such as allergies, cleanliness, and the unpredictable nature of live animals.

To date, the potential benefits of PARO therapy in Hong Kong Chinese have not been systematically examined. Given the successful application of PARO therapy, and the encouraging findings of its positive effects on mood and social interaction and communication, it is suggested that PARO therapy is both feasible and acceptable to elderly people with dementia. Therefore, in this study protocol, we describe the design of a RCT aiming to confirm the findings of our pilot data (see Piloting in the Method section), by providing an evaluation of the effectiveness and benefits of the use of PARO in dementia care in Hong Kong.

The primary objective of the present study is to examine whether robot-assisted intervention using PARO in older Chinese adults with mild to moderate dementia improves mood, and stimulates social interaction and communication compared to psychosocial activities by conducting a methodologically rigorous RCT. Secondary objectives are to examine the effects of PARO therapy on cognitive function, depressive symptoms, and caregiver burden compared to those of psychosocial activities.

**Figure 1 figure1:**
[figure not shown]
PARO, a social robotic seal.

## Methods

### Study Design

This is a single-blind RCT comparing PARO therapy and psychosocial activities in the elderly with dementia. Treatment outcomes will be assessed at baseline (pre-), during, and post-treatment. The study will be carried out in Shatin Hospital, a geriatric day hospital located in Shatin, New Territories, Hong Kong. The protocol for this study was registered with the Australian New Zealand Clinical Trials Registry (ACTRN12614000037606) and has been approved by the Clinical Research Ethics Committee of the Chinese University of Hong Kong. The study design is detailed in Figure 2.

**Figure 2 figure2:**
[figure not shown]
Flow chart of the study design. *Indicates the target number of subjects. CDR: Clinical Dementia Rating, CMAI: Cohen-Mansfield Agitation Inventory, and MMSE: Mini-Mental State Examination.

### Subjects

#### Overview

The study population will include 40 community-dwelling older Chinese adults with mild to moderate dementia. Recruitment will occur through clinical referrals from community dementia day care centres, geriatric outpatient clinics, nurse-led memory clinics, and day hospitals. Those who are potentially eligible will be invited to a face-to-face screening assessment including an elicitation of a medical history, medications, and hospitalization for eligibility confirmation. To be eligible for the study, subjects must meet the inclusion and exclusion criteria described in the following sections.

#### Inclusion Criteria

Community-dwelling older Chinese adults aged ≥60 years will be screened using the Mini-Mental State Examination (MMSE) [36,37]. Those who score between 10-24 with a diagnosis of dementia will be screened for eligibility to the study. Diagnosis of dementia will be based on the Diagnostic and Statistical Manual of Mental Disorders (DSM-IV). Severity of dementia will be determined using Clinical Dementia Rating (CDR), a widely used clinical staging instrument for dementia [38,39]. Subjects with mild to moderate dementia (CDR 1 or 2) will be further assessed for the presence of agitated behaviour using Cohen-Mansfield Agitation Inventory (CMAI) [40].

####  Exclusion Criteria

Individuals who exhibit any behavioural and psychological symptoms of dementia (at least one item of CMAI scoring ≥2) will be excluded from the study. Subjects will also be excluded if they have severe medical conditions which limit their abilities to complete the course of treatment. Concurrent psychotropic medication will be allowed without restriction, but any change in psychotropic prescriptions over the course of the treatment period will be monitored. In addition, those who are currently participating in other studies, experimental therapies, or blinded treatments will be excluded.

### Informed Consent

For eligible individuals, the study will be introduced to the subjects and their caregivers. Written informed consent will be obtained from every eligible subject agreeing to participate, as well as their caregivers prior to the study. If a subject is unable to give written informed consent, proxy consent will be obtained.

### Baseline Assessment and Randomization

After obtaining written informed consent, a baseline (pre-treatment) assessment will be performed. Subjects will be randomized into either the intervention or the control group. A study coordinator will randomize subjects by means of a computer-generated list of random numbers in blocks of six, stratified by gender. Treatment assignments will be concealed in consecutively-numbered sealed envelopes, which will be opened sequentially upon subject enrollment. As it is a single-blind study, the subjects and the study coordinator will not be blinded to the treatment assignment. However, the study coordinator will not take outcome measurements. All investigators and outcome assessors will be blinded to the treatment assignment.

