### Outcome Measures

Measurement of outcomes will take place at pre-, during, and post-treatment. Mood, social interaction, and communication (ie, facial expressions and reactions towards each treatment) will be the primary outcome measures. Secondary outcome measures will include cognitive function and depressive symptoms, as well as caregiver burden. Pre-treatment and post-treatment assessments will be administered by a trained research assistant who will remain blinded to group allocation. Outcome measures administered at each time point are described in Table 1. Attendance at each session will be recorded for all subjects in the study.

**Table 1 table1:** Schedule of assessments.

Assessments	Screening	Pre-treatment	Treatment session number						Post-treatment
			1	2	3	4	5	6	
MMSE^a^	√ ^g^								√
CDR^b^	√								
CMAI^c^	√								
Demographics, lifestyle, and social characteristics		√							
Simplified face scale			√	√	√	√	√	√	
Observation table^d^			√	√	√	√	√	√	
CSDD^e^		√							√
ZBI^f^		√							√
Subjective impression questionnaire			√	√	√	√	√	√	
Qualitative comments from caregivers, facilitator, and therapists									√

^a^Mini-Mental State Examination (MMSE)

^b^Clinical Dementia Rating (CDR)

^c^Cohen-Mansfield Agitation Inventory (CMAI)

^d^Facial expressions and reactions towards each treatment

^e^Cornell Scale for Depression in Dementia (CSDD)

^f^Zarit burden interview (ZBI)

^g^The √ indicates at which point of the study the respective assessments will take place.

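### The only MMSE before treatment is the entry-screening score, taken before consent as written, and the analysis text does not secure its use as a covariate (minor)

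*Protocol article*

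**What the plan says.** All places are in the protocol article.

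- **Role.** The abstract and Outcome Measures list cognitive function, measured by the MMSE, as a secondary outcome. A secondary objective compares it between the arms.
- **Schedule.** Table 1 ticks the MMSE at screening and post-treatment. The other two secondary scales, CSDD and ZBI, are ticked at pre-treatment and post-treatment.
- **Entry.** Inclusion Criteria: "Those who score between 10-24 with a diagnosis of dementia will be screened for eligibility to the study". CDR and CMAI follow as further entry tests and also stand in the screening column of Table 1.
- **Order of steps.** Subjects, Overview: "Those who are potentially eligible will be invited to a face-to-face screening assessment". Informed Consent then introduces the study to eligible individuals: "Written informed consent will be obtained from every eligible subject agreeing to participate, as well as their caregivers prior to the study". Proxy consent is provided for at this same step. Baseline Assessment and Randomization continues: "After obtaining written informed consent, a baseline (pre-treatment) assessment will be performed".
- **Assessor.** Outcome Measures: "Pre-treatment and post-treatment assessments will be administered by a trained research assistant who will remain blinded to group allocation".
- **Analysis.** Statistical Analysis plans unpaired between-group tests (ANOVA or t tests) and an ANCOVA whose named covariates are age and education, with the list left open. It mentions neither baseline MMSE nor an MMSE change score.

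**The concern.** One MMSE score does two jobs: it admits the subject, and it is the only value available as a baseline for the outcome. Two consequences follow.

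1. **Consent.** A person must have MMSE, CDR and CMAI results to be found eligible, and consent is sought only from those found eligible. Read literally, people with dementia undergo study-specific testing, and one outcome value is recorded, before they or a proxy have consented.
2. **Precision.** In a trial of 40, the strongest predictor of post-treatment MMSE is likely to be an earlier MMSE. The text does not commit to adjusting for the one it has, and the pre-treatment visit, where a second could be taken, does not include the test. An unadjusted comparison of post-treatment scores would fit the text and would be the least precise option.

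**Working it through.** **The plan's own figure.** The article gives no sample size for the MMSE. Its calculation concerns the face scale and reproduces with the normal one-sample formula, two-sided: ((1.960 + 1.282) × 0.74 / 0.63)² = 14.5, rounded up to 15 per group; 30 / (1 − 0.25) = 40. It does not bear on this point except to give 15 per arm as the expected number of completers.

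**Order of steps.** Overview: face-to-face screening to confirm eligibility. Inclusion and Exclusion Criteria: eligibility needs MMSE, CDR and CMAI. Informed Consent: asked of eligible people. Baseline section: the pre-treatment assessment follows consent. Taken in sequence, the screening tests precede consent.

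**Inputs for precision**
- Test-retest value .78 (MMSE section), taken as the screening-to-post correlation before selection; .60 and .90 are also tried as assumptions.
- SD 5.9 and mean 16.5 (observation-table reliability sample, n = 11); SD 2.8 and mean 19.3 (pilot, n = 7). Both samples are small and already selected. The SD and mean among people referred are not given, so these are assumptions; SD 4.5 with mean 17, and mean 19.3 with SD 5.9, are also tried.
- Entry cut 10-24.

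**Method.** Simulate observed score = true score + error, with true-score variance SD² × reliability and error variance SD² × (1 − reliability). Round, limit to 0-30, and keep subjects whose screening score is 10-24. Residual SD after adjustment for the screening score = SD(post) × √(1 − r²). Detectable difference at 15 per arm, 80% power, two-sided 5% = (1.96 + 0.8416) × residual SD × √(2/15) = 1.023 × residual SD.

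**Results at reliability .78**

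| Adjustment | Residual SD (SD 5.9, mean 16.5) | Detectable difference | Residual SD (SD 2.8, mean 19.3) | Detectable difference |
|---|---|---|---|---|
| None | 4.77 | 4.88 | 2.69 | 2.75 |
| Screening MMSE | 3.70 | 3.78 | 1.79 | 1.83 |
| Screening + pre-treatment MMSE | 3.33 | 3.41 | 1.61 | 1.65 |

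- **Using the screening score (SD 5.9).** After the cut r = 0.63, so the residual variance is 1 − 0.63² = 0.60 of the unadjusted variance.
- **Adding a second score.** 3.33² / 3.70² = 0.81, a further 19% lower. Over reliability .60-.90 and SD 2.8-5.9 the further reduction is about 14-22%.
- **Replacing the screening score with a fresh one.** Residual variance falls by only about 1-7% over the same range.
- **Effect of the cut itself.** The correlation drops from 0.78 to 0.63 (SD 5.9), but the residual SD is 3.70 with the cut and 3.67 without it. The correlation falls because the spread of scores narrows, not because prediction gets worse.
- **Regression to the mean.** At SD 5.9 and reliability .78, the expected change from screening to post-treatment without any treatment effect is −0.07, 0.14, 0.42 and 0.69 points for assumed referral means of 16.5, 18, 20 and 22. It arises equally in both arms, and the simulated between-arm difference in change is about 0.

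**The case against.** - **There is no contradiction with the baseline sentence.** A reader might infer that Table 1 breaks the promise of a baseline after consent. It does not: that sentence names no instruments, and Table 1 has a pre-treatment column with demographics, CSDD and ZBI. Study Design and Outcome Measures say in general terms that outcomes are measured before, during and after treatment; Table 1 specifies this by instrument. This stands.
- **The comparison is not biased.** A reader might fear that selecting on the score distorts the MMSE result. Screening precedes randomization, so the drift is equal in expectation in both arms, and no within-arm MMSE test is planned. This stands. For the same reason it does not matter who gives the screening test, since nobody is yet allocated.
- **The entry cut does not waste precision.** This also stands, as the residual SDs of 3.70 and 3.67 show. The 14-22% gain comes from a second measurement and would be available in most trials; it does not measure damage done by the cut.
- **An article condenses.** A separate screening consent or assent, the allowed interval from screening to treatment, and the full covariate list may stand in the full protocol or analysis plan. The interval is therefore not raised here. The covariate list is open-ended, so baseline MMSE is not excluded. The consent sequence is different, because the article states it. Ethics approval and the statement that consent comes before the study do not change an order in which eligibility is already known when consent is asked.
- **Using the screening score spares people with dementia a further test.** This is fair, and is why repeating the MMSE is a preference and not a requirement.

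**Conclusion.** The point holds as a minor one. The MMSE's only value before treatment is the score that decides entry, and as written that testing, with CDR and CMAI, precedes consent or proxy consent. The documents support neither bias in the randomized comparison nor a loss from the 10-24 cut, and they do not say that the MMSE comparison uses the screening score at all. What is shown is available precision that the text does not secure: a residual SD of about 4.8 unadjusted against 3.7 with the screening score (SD 5.9, reliability .78), or 2.7 against 1.8 with the pilot SD of 2.8. A second score would lower residual variance by a further 14-22%. The within-arm drift of about −0.1 to +0.7 points matters only if change within an arm is reported as an effect. The sizes rest on an assumed referral mean and SD, and on taking .78 as the screening-to-post correlation; a long gap between screening and treatment would weaken the screening score. The outcome is secondary.

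**What to change.** 1. Obtain consent, or proxy consent, before the study-specific screening assessment (MMSE, CDR, CMAI). If a separate screening consent exists, say so in Informed Consent. Cost: consent is sought from some people who then fail screening.
2. State that post-treatment MMSE is compared by ANCOVA with the screening MMSE as a covariate. Cost: none, as the score is already collected.
3. Preferably, add one MMSE at the existing pre-treatment visit, given by the blinded research assistant already assigned to it, and use it as a second covariate beside the screening score. Keep the screening score for eligibility. Cost: one more short test per subject and one more practice exposure, the same in both arms.
4. If step 3 is declined, say in Table 1 or Outcome Measures that the screening MMSE is the baseline for this outcome, and do not present within-arm MMSE change as a treatment effect.

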### Intervention Group

The PARO therapy will take place for 30 minutes once a week over a six week period, and will be delivered in a quiet room that is isolated from the common unit (ward) in the Occupational Therapy Department of Shatin Hospital, with minimal environmental distractions. The number of sessions, the length of each session, and the time frame of this study were decided based on the results of our pilot study (see Piloting of this section) and other PARO intervention studies which reported small or significant changes in mood, social interaction, and communication [15]. Given this, one 30-minute session per week for six consecutive weeks would allow sufficient time for identifying significant changes, and would also reduce the burden of commitment for subjects.

The PARO therapy will be delivered in a structured, small-group approach, in which a group of three to four subjects will be arranged to sit around a table with PARO in the centre. The subjects in each group can be substituted by subjects from other groups to optimize the chance of conducting each session. A facilitator who is familiar with the PARO caregiver’s manual will deliver the PARO therapy. Research team therapists will train the facilitator and monitor the sessions.

The PARO therapy is based upon a standardised framework, and involves activities around the concepts of engaging, social interaction, and communication. There are six stages/themes, including (1) introducing PARO, (2) baby-sitting PARO, (3) grooming PARO, (4) feeding PARO, (5) making over PARO, and (6) wardrobe PARO. During each session, the facilitator will show PARO to each subject and demonstrate how PARO responds. Subjects will be encouraged to touch and hold PARO, describe the features and appearance of PARO, and help take care of PARO. The session will proceed for at least 30 minutes. With one session per week, there will be at least a total of 180 minutes of the treatment in the six week period.

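### A single published block size of six per gender stratum makes about 21-23% of the 40 assignments certain to anyone who tracks past ones: a residual risk, cheaply reduced

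*Protocol article*

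**What the plan says.** Under Baseline Assessment and Randomization, the protocol article fixes the method: "A study coordinator will randomize subjects by means of a computer-generated list of random numbers in blocks of six, stratified by gender". Concealment is specified in the next sentence: "Treatment assignments will be concealed in consecutively-numbered sealed envelopes, which will be opened sequentially upon subject enrollment". On blinding it says: "As it is a single-blind study, the subjects and the study coordinator will not be blinded to the treatment assignment". Two safeguards follow: "However, the study coordinator will not take outcome measurements" and "All investigators and outcome assessors will be blinded to the treatment assignment". The same section describes the baseline assessment, after consent, before it describes randomization.

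Elsewhere the article gives one site (Study Design), 40 subjects recruited by clinical referral (Subjects), and a sample size that is equal per group (Sample Size Calculation). Treatment is given in small groups. One facilitator serves both arms (Control Group), and on supervision the Intervention Group section says: "Research team therapists will train the facilitator and monitor the sessions".

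The allocation ratio is not stated. Nor does the article say who confirms eligibility or who decides when a subject is enrolled.

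**The concern.** A sealed envelope hides the next assignment but not the earlier ones. With every block the same known length, the earlier ones determine the end of each block: once three subjects in a block have gone to one arm, the rest must go to the other. Here the earlier assignments are visible to several people. The coordinator and the subjects are unblinded, and the facilitator and the therapists who monitor sessions see which treatment is given.

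Foreknowledge matters only if it can influence who enters and when. There is some room for that, because entry is by referral and the exclusion for severe medical conditions that limit completion of treatment calls for judgement. In a trial of 40, with a self-reported face scale among the primary outcomes, steering a few subjects could shift the comparison. Covariate adjustment cannot correct for selection on features that were not measured.

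**Working it through.** **Inputs.** From the article: block size 6, two gender strata, one site, 40 subjects. Assumed: 1:1 allocation (suggested by equal group sizes), and an observer who knows the block size and every earlier assignment in the stratum. The gender split is not given, so all splits were examined.

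**The plan's own figure.** The article states no predictability figure. Its total does reproduce: 15 per group in two groups is 30, and 30 / (1 - 0.25) = 40.

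**One complete block of six (3:3).** There are C(6,3) = 20 equally likely orders. An assignment is certain once one arm has its three.
- Positions 1 to 3: never certain.
- Position 4: certain if the first three match, 2/20 = 0.1.
- Position 5: certain if the first four split 3:1, probability 0.4.
- Position 6: always certain, 1.0.

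The sum is 0.1 + 0.4 + 1.0 = 1.5 of 6, or 25%. The closed form for a block of 2m agrees: 2m/(m+1) = 6/4 = 1.5.

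**Forty subjects in two strata.** Incomplete last blocks lower the share.

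| Gender split | Larger (or first) stratum | Other stratum | Certain of 40 | Share |
|---|---|---|---|---|
| 28/12 | 4 blocks + 4: 6.0 + 0.1 = 6.1 | 2 blocks: 3.0 | 9.1 | 22.75% |
| 20/20 | 3 blocks + 2: 4.5 | 3 blocks + 2: 4.5 | 9.0 | 22.5% |
| 35/5 | 5 blocks + 5: 7.5 + 0.5 = 8.0 | 5 only: 0.5 | 8.5 | 21.25% |

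Over all splits the range is 8.5 to 9.1 of 40, or about 21.3% to 22.8%.

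**Best guess.** An observer who always names the arm with more places left in the block is expected to be right 3 + (2^6/20 - 1)/2 = 3 + 1.1 = 4.1 times in 6, or 68.3%. For 40 subjects the range is 66.8% to 67.5%, against 50% by chance.

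**Randomly mixed block sizes.** These were simulated with an observer who knows the set of sizes but not their order.
- 20 per stratum: certain share 22.4% with fixed six, 5.9% with sizes 4 and 6. Best-guess accuracy is about 67% and 69%.
- 28/12: certain share 22.7% with fixed six, 6.1% with sizes 4 and 6.

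**Price in balance, 28/12 split.** With fixed six, only the four left-over subjects can be unbalanced. They split 3:1 with probability 0.4, so the mean imbalance is 0.4 x 2 = 0.8 subjects and the maximum is 2. With sizes 4 and 6 the simulated mean is 0.83 and the maximum 4. The comparison depends on the split: at 20/20, fixed six can already reach 2 + 2 = 4.

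**The case against.** The strongest reply is that exploiting the blocks needs one person who both knows every earlier assignment in a stratum and influences who enrols or when, and the article names no such person. The coordinator randomizes but is not said to screen or judge eligibility. Therapists monitor sessions but are not said to recruit. Referrers are not said to see assignments, and a subject knows little beyond his or her own group. The investigators are stated to be blinded. All of this stands, and it is why the point is a vulnerability and not evidence of selection. The blinding statement has a limit: by the Observation Table section, whoever codes the videotapes sees which treatment is being given. But coders are not said to enrol subjects either.

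A reader might infer that the trial is open-label. It is not: it is described as single-blind, with investigators and outcome assessors blinded. A reader might also infer that concealment has failed. Numbered sealed envelopes opened in sequence are specified, and baseline assessment is described first, so the documents do not support that. Nor does the 21-23% describe a coordinator reading the list. Anyone who could read it would know every assignment at any block size. The figure belongs only to someone who counts.

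It is also fair to say that varying the blocks does not improve average guessing, and that who generates the list or prepares the envelopes is detail an article may leave to the full protocol. Both stand. The block size itself, however, is stated in the article and can be judged.

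**Conclusion.** The point holds as a minor to moderate weakness in a stated design choice. With one published block size per gender stratum, about nine of the 40 assignments could be known in advance with certainty by someone tracking the earlier ones, and the envelopes cannot prevent this.

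That figure rests on 1:1 allocation, knowledge of the block size and complete tracking by stratum. Whether such a person has any say over enrolment is not settled by the article. The effect on the face-scale comparison has not been quantified and cannot be from what is given, so no claim is made that the result would be biased by any particular amount.

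**What to change.** For subjects not yet randomized, replace the fixed blocks of six with block sizes chosen at random (for example 4 and 6) within each gender stratum. Do not disclose the sizes to anyone who refers, screens or enrols. Add a sentence stating that the unblinded coordinator does not decide eligibility or the order of enrolment; this matters because varied blocks remove certainty but leave the best guess about as good as before.

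The cost is a new list, new envelopes and a small change of text, with no extra subjects or visits. The statistical downside is a slightly larger possible final imbalance: for an assumed 28/12 gender split, a maximum of about 4 subjects instead of 2, with the mean almost unchanged. The article expects the last post-treatment assessment in 2015 and does not say how many subjects remain to be randomized, so the benefit depends on that number.
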